### Sample Size

Based on a Japanese study [21], the mean change in VAS after 52 weeks with 1 mg dienogest was –52.1 (SD 24.13) for secondary dysmenorrhea. In the Japanese phase II dose-finding study, [19] the average change in VAS was –35.74 at 0.25 mg×2, –44.31 at 0.5 mg×2, and –50.78 at 1 mg×2 at 12 weeks. Therefore, it is assumed that at least an effect of 0.25 mg×2 or more can be expected by this test administration, and the noninferiority margin is set to 15. It is assumed that the effects of the 1 mg group and the 2 mg group are similar, and SD is assumed to be 24.13 with reference to the Japanese phase III study. [22] In the above setting, 41 cases in each group (82 cases in total) are required to achieve a power of 80% at a one-sided significance level of 2.5%. When 5% of dropout cases are added to each group, the required sample size becomes 44 cases in each group (88 cases in total).

We evaluated the incidence of low estrogen symptoms during the study treatment period as an important secondary endpoint. On the basis of the long-term use of dienogest [23], we assumed the incidence proportion for dienogest 1 mg/day and 2 mg/day to be 20% and 50%, respectively, with the chi-squared test providing more than 80% power at a 2-sided significance level of 5%. Therefore, the sample size in this study (88 cases in total) is also sufficient to assess the incidence of low estrogen symptoms.

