### Statistical Analysis

The primary analysis involves comparing the change in VAS from baseline to 48 weeks between the dienogest 1 mg/day group and 2 mg/day group using the mean difference and its 95% CI. When the lower limit of confidence exceeds –15 (noninferiority margin), the noninferiority of the effect of the 1-mg group to the 2-mg group will be recognized.

For the secondary efficacy endpoint, each of the dienogest 1 mg/day group and the 2 mg/day group will be compared to estimate the difference and its 95% CI for the mean value of dysmenorrhea score and change in endometriotic cyst size from baseline to 48 weeks.

In the safety evaluation, the frequency of low estrogen symptoms during the study treatment period is aggregated, and a 95% CI is calculated that is based on a normal approximation of the binomial distribution. In addition, a chi-square test will be used to compare groups. The 2-sided significance level is 5%.

The frequencies of the occurrence of adverse events and side effects are calculated for the safety analysis target population. As a secondary safety analysis, each of the dienogest 1 mg/day group and 2 mg/day group will be compared to estimate the difference and its 95% CI for the mean value of bone density, Kupperman score, and estrogen concentration. Statistical analyses are performed by R (version 4.1.0; R Foundation for Statistical Computing).

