## Discussion

### Principal Findings

This study aims to demonstrate that dienogest 0.5 mg tablets are as effective and safe as dienogest 1-mg tablets in the treatment of endometriosis. Furthermore, based on the evaluation results from this study, recommendations for the optimal use of dienogest 0.5-mg and 1-mg tablets could be proposed.

Currently, 0.5 mg dienogest tablets are approved for dysmenorrhea, but their effectiveness in improving endometriosis symptoms and lesions remains unclear.

Osuga et al [19] conducted a study comparing dienogest 1 mg/day and 2 mg/day in patients with primary dysmenorrhea and reported equivalent improvements in VAS scores between the 2 groups. However, this study did not include patients with endometriosis-related dysmenorrhea, making it insufficient to evaluate the efficacy of dienogest for endometriosis.

Another study by Osuga et al [22] compared dienogest 1 mg/day with placebo and demonstrated its efficacy in treating dysmenorrhea. However, only approximately 23% of the study population had endometriosis, which is insufficient to fully assess its effectiveness for this condition. Currently, there are no other studies comparing dienogest 0.5-mg tablets with 1-mg tablets for endometriosis, and thus, the findings of this study are expected to provide novel insights into the efficacy and safety of dienogest 0.5-mg tablets for endometriosis.

With respect to serum estrogen levels during dienogest administration, it was observed that estrogen levels did not decrease significantly with a 1 mg/day dosage compared with the placebo group. However, a dose-dependent reduction in estrogen levels was observed [19,24].

Prolonged hypoestrogenic states induced by dienogest therapy may increase the risk of adverse effects such as bone mineral density loss. Estrogen plays a crucial role in maintaining bone homeostasis by promoting osteoblast activity and inhibiting bone resorption by osteoclasts [25].

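### The 80% power holds only if the two doses are exactly equal, while the figures that set the margin put 1 mg/day 6.47 points behind, where power is about 35–38%

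*Protocol article*

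**What the plan says.** All the planning figures are in the Sample Size section of the protocol article.

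- **Source data.** For the Japanese phase II dose-finding study, "the average change in VAS was –35.74 at 0.25 mg×2, –44.31 at 0.5 mg×2, and –50.78 at 1 mg×2 at 12 weeks".
- **Margin.** From these figures the plan reasons that the tested dose should do at least as well as 0.25 mg×2, and "the noninferiority margin is set to 15".
- **Assumed true difference.** "It is assumed that the effects of the 1 mg group and the 2 mg group are similar", with an SD of 24.13.
- **Result.** "41 cases in each group (82 cases in total) are required to achieve a power of 80" percent at one-sided 2.5%. With 5% dropout this becomes 44 per group.

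The trial arms are 0.5 mg twice daily (1 mg/day) and 1 mg twice daily (2 mg/day), according to Data Collection and Study Procedures. The decision rule in Statistical Analysis reads: "When the lower limit of confidence exceeds –15 (noninferiority margin"), noninferiority is recognized.

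The Discussion (Principal Findings) says that the same dose-finding study "reported equivalent improvements in VAS scores between the 2 groups". It gives the trial's aim as demonstrating that the 0.5-mg tablets match the 1-mg tablets in effectiveness and safety.

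**The concern.** One row of figures is used for the margin but not for the expected difference. The outer two values give the margin. The upper two values are the doses actually being compared, and they differ by 6.47 against 1 mg/day. The plan then takes the two doses as similar and does not mention this gap or say why it can be ignored.

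Two readings of the eventual result are at stake.

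- **A failure.** If noninferiority is not shown, a reader who takes 80% power at face value may see evidence that 1 mg/day is inferior. It may only reflect a modest true deficit in a trial with little power at that deficit.
- **A pass.** The margin is the whole quoted gap between 2 mg/day and 0.25 mg×2. A pass therefore excludes a deficit of 15 or more. That is a weaker statement than the equal effectiveness named as the aim in the Discussion.

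**Working it through.** **Inputs.** From Sample Size: margin 15; SD 24.13; one-sided 2.5%; power 80%; 41 evaluable and 44 enrolled per group; mean changes −35.74 (0.25 mg×2), −44.31 (0.5 mg×2) and −50.78 (1 mg×2). From the Abstract: 1:1 allocation. The changes exceed 10, so I take the unit to be points on a 0–100 scale. A deficit is written below as a positive number of points by which 1 mg/day is worse.

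**1. Reproduce the plan's figure (true difference 0).**

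n = 2 × (1.960 + 0.8416)² × 24.13² / 15² = 2 × 7.849 × 582.3 / 225 = 40.6, so 41 per group. Then 41 / 0.95 = 43.2, so 44. Both match.

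**2. Check what similar means in the calculation.** At a true deficit of 1, n = 2 × 7.849 × 582.3 / 14² = 46.6, so 47 per group. The stated 41 therefore uses a difference of exactly 0.

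**3. Differences in the quoted row.**

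- 50.78 − 35.74 = 15.04, which matches the margin.
- 50.78 − 44.31 = 6.47, the gap between the two trial doses.
- 6.47 / 15 = 43% of the margin.

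**4. Power by true deficit d.**

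Standard error = 24.13 × √(2/n) = 5.33 at n = 41 and 5.14 at n = 44.

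Normal approximation: power = Φ((15 − d)/SE − 1.96). At d = 6.47 and n = 41, this is Φ(8.53/5.33 − 1.96) = Φ(−0.36) = 36%. The t-test columns use the noncentral t distribution.

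| True deficit | t-test, n = 41 | t-test, n = 44 | normal, n = 41 | normal, n = 44 |
|---|---|---|---|---|
| 0 | 79.4% | 82.2% | 80.4% | 83.0% |
| 2 | 67.4% | 70.5% | 68.4% | 71.5% |
| 3 | 60.4% | 63.6% | 61.5% | 64.5% |
| 5 | 45.8% | 48.5% | 46.7% | 49.4% |
| 6.47 | 35.2% | 37.4% | 36.0% | 38.1% |

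**5. Where power falls below one half.** This happens at d = 15 − 1.96 × SE: 4.6 at n = 41 and 4.9 at n = 44 (4.4 and 4.8 with the t critical value).

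**6. Scale of the gap.** For 80% power at 6.47, n = 2 × 7.849 × 582.3 / 8.53² = 125.6, so 126 evaluable per group. This is shown for scale only.

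**7. What an observed 6.47 would do.** The 95% half-width at the assumed SD is 10.6 (n = 41) or 10.2 (n = 44). An observed deficit of 6.47 would give a lower limit of about −17.1 or −16.7, which is beyond −15.

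**8. Sensitivity to the SD (assumed range).** With 41 per group and a deficit of 6.47, normal-approximation power is 49% at SD 20 and 28% at SD 28.

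**The case against.** **The arithmetic is right and the premise is stated.** The 41 and 44 reproduce, and the similarity assumption stands directly before the sample size. Zero difference is a common planning assumption for noninferiority. This stands: a reader who infers a sample-size error would be mistaken. A condensed article may also leave a table of power under alternatives to the full protocol. What remains is that the article itself prints figures that disagree with its assumption and gives no reason for preferring the assumption.

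**The 6.47 is weak evidence.** It is a 12-week point estimate with no standard error or arm sizes, from a study the Discussion describes as primary dysmenorrhea. If that study had SD 24.13 (an assumption), 6.47 would reach two-sided 5% significance only with about 107 per arm: 2 × (1.96 × 24.13 / 6.47)² = 106.9. This stands, so 6.47 cannot be treated as the expected effect. The margin does rest on the same 12-week data, however, and power is already down to 60–64% at a deficit of 3.

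**Another planning figure points the other way.** Sample Size also quotes −52.1 after 52 weeks with 1 mg dienogest in secondary dysmenorrhea, which is closer to this trial in duration and condition. Set against −50.78, it would favour 1 mg/day by 1.32, giving about 86% power with 41 per group. But it has no concurrent 2 mg/day comparator, and the dose is ambiguous: Limitations says no earlier study examined 1 mg/day beyond 12 weeks. The plan does not offer it as the reason for similarity. It shows only that the planning evidence is mixed.

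**The trial is therefore more likely to fail than succeed.** A reader might infer this from the table. The documents do not support it: it holds only if the true deficit exceeds about 4.6 to 4.9, and nothing shown establishes that.

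**The Discussion misreports the dose-finding study.** This is also tempting, but the study is not shown, and it may have concluded equivalence despite different point estimates. The documents support only a request to reconcile the two accounts.

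**The loose wording does not alter the decision rule.** Statistical Analysis claims noninferiority only, and Study Objectives speaks of a comparison. This is true, and the correction is confined to the aim as worded in the Discussion.

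**Conclusion.** The point holds as an unqualified power claim, not as a calculation error. The 80% is correct at a true difference of 0 and falls quickly below it: about 60–64% at a deficit of 3, and 35–38% at the 6.47 the article itself quotes, across both formulas and 41 to 44 evaluable per group. These figures rest on SD 24.13, one-sided 2.5%, an unadjusted comparison of mean changes, and at most the planned dropout. The 6.47 is one plausible scenario at the unfavourable end of the range 0 to 6.47.

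Separately, a pass supports only the statement that 1 mg/day is less than 15 VAS points worse than 2 mg/day. That leaves room for a deficit of almost the whole quoted gap to 0.25 mg×2, so it does not establish equal effectiveness.

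**What to change.** No further enrolment is proposed. The text changes are:

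1. **Sample Size.** State that 80% power applies only at a true difference of 0. Give power across 0 to 6.47, for example 79–82% at 0, 60–64% at 3 and 35–38% at 6.47. Give the reason for assuming similarity, including how the 6.47 and the −52.1 were weighed.
2. **Principal Findings, account of the dose-finding study.** Reconcile "reported equivalent improvements in VAS scores between the 2 groups" with the 6.47 quoted from the same study in Sample Size. Printing the observed difference beside the study's reported conclusion is enough.
3. **Principal Findings, aim.** Replace the wording of equal effectiveness with what the rule supports: 1 mg/day is less than 15 VAS points worse than 2 mg/day, with a note that 15 is the whole quoted gap to 0.25 mg×2.

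The cost is wording only, and the stated power will look less favourable.

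Optionally, the primary comparison could be adjusted for baseline VAS, which the change-from-baseline endpoint already requires, to gain precision. The size of the gain cannot be worked out from the document. This is not a text edit: Statistical Analysis specifies a mean difference with its 95% CI, the trial is open-label, and Results says data collection is finalised. It would have to be fixed and documented before any analysis of the data by arm.

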### Ethical Considerations

The study protocol was approved by the accredited clinical research review committee of the Naoya City University Hospital Clinical Research Review Board (approval number 2021A001-23b001). Informed consent was obtained from all participants before their enrollment. Researchers must ensure that all patients who have provided written informed consent meet the inclusion criteria and do not meet any of the exclusion criteria. The study adheres to the ethical principles of the Declaration of Helsinki. All data are anonymized to protect participant privacy. No personally identifiable information is included in the dataset. In addition, stringent protective measures such as encrypted data storage and restricted access protocols have been implemented to ensure data confidentiality.

## Results

Participant enrollment for the trial has been completed. The first participant was enrolled in August 2021, and a total of 88 participants have been enrolled, with 44 participants allocated to each group (Figure 1). As of March 22, 2025, data collection has been finalized and is currently being fixed for analysis. Study flowchart showing the allocation of participants, in accordance with the CONSORT (Consolidated Standards of Reporting Trials) checklist (Multimedia Appendix 4).

**Figure 1 figure1:**
[figure not shown]
CONSORT (Consolidated Standards of Reporting Trials) flowchart. DNG: dienogest.

## Discussion

### Principal Findings

This study aims to demonstrate that dienogest 0.5 mg tablets are as effective and safe as dienogest 1-mg tablets in the treatment of endometriosis. Furthermore, based on the evaluation results from this study, recommendations for the optimal use of dienogest 0.5-mg and 1-mg tablets could be proposed.

Currently, 0.5 mg dienogest tablets are approved for dysmenorrhea, but their effectiveness in improving endometriosis symptoms and lesions remains unclear.

Osuga et al [19] conducted a study comparing dienogest 1 mg/day and 2 mg/day in patients with primary dysmenorrhea and reported equivalent improvements in VAS scores between the 2 groups. However, this study did not include patients with endometriosis-related dysmenorrhea, making it insufficient to evaluate the efficacy of dienogest for endometriosis.

Another study by Osuga et al [22] compared dienogest 1 mg/day with placebo and demonstrated its efficacy in treating dysmenorrhea. However, only approximately 23% of the study population had endometriosis, which is insufficient to fully assess its effectiveness for this condition. Currently, there are no other studies comparing dienogest 0.5-mg tablets with 1-mg tablets for endometriosis, and thus, the findings of this study are expected to provide novel insights into the efficacy and safety of dienogest 0.5-mg tablets for endometriosis.

With respect to serum estrogen levels during dienogest administration, it was observed that estrogen levels did not decrease significantly with a 1 mg/day dosage compared with the placebo group. However, a dose-dependent reduction in estrogen levels was observed [19,24].

Prolonged hypoestrogenic states induced by dienogest therapy may increase the risk of adverse effects such as bone mineral density loss. Estrogen plays a crucial role in maintaining bone homeostasis by promoting osteoblast activity and inhibiting bone resorption by osteoclasts [25].

In a study by Momoeda et al [12], bone density changes were measured at 24 and 52 weeks following the administration of 2 mg/day of dienogest. There was a significant reduction in bone mass at both time points (mean –1.6%, SD 2.4%; *P*<.001; mean –1.7%, SD 2.2%; *P*<.001), though the decrease was concluded to be mild. According to Seo et al [13], after one year of administering dienogest 2 mg/day, lumbar spine bone mineral density decreased by 2.2% at 6 months and by 2.7% after 1 year compared to baseline. Furthermore, 75% (45/60) of women experienced significant bone mineral density reduction after one year. Given the high likelihood that dienogest-induced bone density reduction is correlated with estrogen levels [15], it is anticipated that the 1 mg/day group in this study will exhibit less bone loss.

While bone density reduction has been the primary focus of existing studies, other low estrogen symptoms, such as vasomotor symptoms, mood changes, and cardiovascular risks, also warrant evaluation in the context of long-term dienogest administration. Although the frequency of these symptoms is expected to be low with dienogest therapy, this study will assess the incidence and severity between the 1 mg/day and 2 mg/day groups. By analyzing these differences, this study aims to clarify whether dosage variations influence adverse effects beyond bone density reduction and provide insights into dose selection for the treatment of endometriosis-associated dysmenorrhea.

### Limitations

This study has several limitations. First, only patients with ovarian endometriotic cysts were included, excluding cases of endometriosis without ovarian involvement. This selection criterion was implemented to ensure diagnostic accuracy and maintain a homogeneous study population. However, future studies may be needed to evaluate the effects of long-term dienogest therapy in patients with other forms of endometriosis.

Second, as it was not conducted as a double-blind trial, there is a potential risk of bias in VAS and dysmenorrhea score evaluations.

This study was conducted within the framework of Japan’s health insurance system, which required specifying the prescribed drug formulation (0.5-mg or 1-mg tablet). Consequently, blinding was not feasible, and an open-label design was adopted. To minimize bias, we implemented 3 key measures. First, objective assessments, including ultrasound imaging, hormone levels, and bone density, were incorporated as primary endpoints to reduce reliance on subjective pain evaluations. Second, centralized randomization via an electronic data capture system was used to eliminate selection bias. Third, covariate adjustment for age and adenomyosis presence ensured balanced group allocation. These strategies enhance the study’s validity and reliability.

Given that endometriosis often requires long-term treatment until menopause, evaluating the efficacy and safety of extended dienogest administration is crucial. Although the observation period of this study is limited to 48 weeks, it provides valuable data, as no previous study has examined the effects of 1 mg/day beyond 12 weeks. Further research with extended observation periods is necessary to assess long-term efficacy and safety.

### Conclusions

This study will enable us to evaluate the efficacy and safety of the dienogest dosage over 48 weeks and provide a more precise and safer treatment for patients with endometriosis.

After the completion of the study, the treatment of endometriosis and assessment of side effects in enrolled patients will continue. The findings from this study will be disseminated through conference presentations and academic publications to contribute to the ongoing refinement of treatment strategies for endometriosis.

## Appendix

Multimedia Appendix 1 SPIRIT (Standard Protocol Items: Recommendations for Interventional Trials) checklist.

Multimedia Appendix 2 This figure shows the medical questionnaire for the first visit.

Multimedia Appendix 3 This figure shows the medical questionnaire for the 2nd and subsequent visits.

Multimedia Appendix 4 CONSORT (Consolidated Standards of Reporting Trials) checklist.

## Abbreviations

CONSORT: Consolidated Standards of Reporting Trials
SPIRIT: Standard Protocol Items: Recommendations for Interventional Trials
VAS: visual analog scale
